**Figure 2. f2:**
[figure not shown]
Study schema.

### Selection of study population

All patients aged 65 or older attending the GP site investigator will be screened for eligibility by the GP. Patients meeting all of the inclusion criteria and none of the exclusion criteria will be eligible for inclusion.

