### Feasibility study

Feasibility of the exercise component of the intervention was assessed in a study in 2019 and 2020
^12^. The findings have been key to refining the intervention for this RCT. We offered an exercise intervention to reverse frailty and build resilience in primary care consultations. We set out to assess uptake of the exercise regime; ratings of its ease and subjective health after participation; how a follow-up telephone-call might affect compliance and overall feasibility. We applied the Bowen feasibility model
^13^ which has been successfully used in assessing public health and preventive medicine interventions. This feasibility model tests eight areas of focus: acceptability; demand; implementation; practicality; adaptation; integration; expansion; and limited-efficacy testing. Selected results include:

A total of 94 of 107 eligible people (88%) participated (average age 77, 59 females (63%)). 95% of females and 78% of males enrolled. Only 15% had previously considered resistance exercises.

Participants found the exercises both easy to follow and generally easy to do. Overall, 32% described exercises as ‘very easy’, 55% ‘somewhat easy’, 7% ‘neither easy nor hard’, 6% ‘somewhat hard and 0% ‘very hard’.

At one month, 66% of participants called were exercising regularly (76% of females, 50% of males). At two months, compliance among those who had not been called at one month was: 65% (67% of females, 62% of males). However, compliance among those previously called was higher: 78% (88% of females, 63% of males). 64% of those who were not doing exercises at one month had taken them up following the single phone call (67% of females, 63% of males).

Many described how the home-based exercises helped with staying active and reducing anxiety while housebound during the Covid-19 pandemic

The majority of participants self-reported their general health had improved as a result of doing the exercises and none reported feeling worse. 14% felt ‘much better’, 52% ‘slightly better’, 34% ‘about the same’, 0% ‘slightly worse’, and 0% ‘much worse’

Each of the eight areas of focus of the Bowen feasibility model have been addressed and satisfy overall feasibility. Publication of this feasibility study is pending.

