### Public and patient involvement

Public and patient involvement in health involves undertaking research with members of the public rather than for them. As PPI has been a key consideration within Irish health research culture, we wanted to enable the involvement of potential participants’ in co-designing our RCT to ensure that their priorities were at its core. We built on two group discussions with 24 over 65-year olds, when introducing an exercise regime in a previous service evaluation study
^14^, and 145 one-on-one discussions listening to feedback during the feasibility study. We wished to learn additionally from participants in three online workshops to optimise our patient communication model, refine the exercise regime and develop dietary guidance for a future trial.

We convened three online group workshops with older adults involved in the feasibility study. The group size of an average of 5 participants and 2 researchers was in keeping with best practice for conducting both group-based action learning
^15^ and focus group activity
^15,
16^. Key themes and questions for each workshop were prepared in advance. A Socratic approach of open questions with active listening was used in order to ensure the voices of the non-researchers are primarily heard. Transcripts were analysed and key feedback synthesised under the headings of: ‘patient engagement and communication model’, ‘exercise regime’ and ‘dietary guidance’. Analysis used both an inductive and deductive approach drawing on normalisation process theory. Our approach was guided by a framework for effective and meaningful public and patient representative (PPR) involvement in health research
^17–
19^, which includes operating in a structured environment; managing expectations and ensuring roles are clear; providing support for successful participation and ensuring inclusive representation; and commitment to co-learning involving institutional leadership.

PPI output included strong endorsement from participants for offering this intervention; co-design of the patient communication model; inclusion of preferred setting, medium and gender balance for the exercise regime; and co-design of the dietary guidance content.

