***Inclusion criteria***

 Aged 65 or older at baseline Rockwood clinical frailty scale score 4 or 5 (vulnerable or mildly frail) Able and willing to provide informed consent and to comply with the requirements of this study protocol

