***Exclusion criteria***

 Rockwood clinical frailty scale score > 5 End of life care Persons in residential care home Concurrent malignancyChronic kidney disease, stage 3 or 4 Coded diagnosis of severe dementia as per GP or consultant geriatrician diagnosis or baseline Montreal Cognitive assessment (MoCA) score ≤ 10 Persons unable to engage in discussion on frailty due to acute care needs or determined to be inappropriate by GP (e.g., needing transfer to ED or acutely unwell or disorders resulting in intolerance of the intervention) Subjects unable to provide written informed consent

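### The eligibility criteria do not exclude, and the baseline data do not record, people who already received the exercise component in the 2019–2020 feasibility study, so carry-over is possible

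*Protocol article*

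**What the plan says.** The entry rule is broad. Under Selection of study population, "All patients aged 65 or older attending the GP site investigator will be screened for eligibility by the GP", and "Patients meeting all of the inclusion criteria and none of the exclusion criteria will be eligible for inclusion". The inclusion criteria cover age, the Clinical Frailty Scale (CFS) ("Rockwood clinical frailty scale score 4 or 5 (vulnerable or mildly frail") and consent with willingness to comply. The nearest exclusion is "Persons unable to engage in discussion on frailty due to acute care needs or determined to be inappropriate by GP", and its examples are acute illness, emergency transfer and intolerance of the intervention. Neither list mentions earlier receipt of the programme.

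The Feasibility study section reports that "Feasibility of the exercise component of the intervention was assessed in a study in 2019 and 2020". It was offered in primary care consultations, and 94 of 107 eligible people took part, at an average age of 77. At two months, 65% of those not telephoned earlier and 78% of those telephoned were exercising. The section on public and patient involvement adds: "We convened three online group workshops with older adults involved in the feasibility study".

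Enrolment was due to begin in December 2020 (Dissemination). The baseline measurements under Study methods, assessments and procedures contain no item on earlier exposure to the programme. The primary mixed model under Efficacy analysis uses arm, baseline SHARE-FI, age and a practice effect, with no term for prior exposure.

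**The concern.** The trial compares offering the programme with not offering it. A person who received the exercise component a year or so earlier supplies less of that contrast than a new participant. In the usual care arm they may still be doing the exercises. In the intervention arm, part of what the exercises can achieve may already be in their baseline SHARE-FI and muscle mass. Either way the arms move closer together, and a null result could not be separated from carry-over, because exposure is not recorded.

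This is not a detail left to an analysis plan. The eligibility lists are printed in full and decide who is randomised, and no later analysis can recover an exposure that was never collected. The feasibility participants were known to the team, fall in the trial's age range and were recruited in the same kind of setting.

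**Working it through.** **Step 1: can a feasibility participant be enrolled?** Such a person who is 65 or older, scores CFS 4 or 5, consents and has none of the listed exclusions meets the entry rule as printed. Nothing in the criteria stops enrolment, and nothing in the baseline list would show it had happened.

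**Step 2: reproduce the planned sample size.** Inputs from Determination of sample size: 15% v 3% reaching non-frail, 1:1 allocation, type I error 0.05 (taken as two-sided, which the protocol does not state), power 80%, 15% dropout. With pooled variance and no continuity correction,

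n per arm = [1.960·√(2·0.09·0.91) + 0.842·√(0.15·0.85 + 0.03·0.97)]² / 0.12² = 88.09.

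The stated 176 is 2 × 88. Rounding up gives 178, and 178/0.85 = 209.4, so 210 enrolled. The plan's figures reproduce.

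**Step 3: power with no overlap.** At 88 per arm the normal approximation gives 79.96%. Full binomial enumeration of the uncorrected chi-square test gives 83.5%. The rows below use enumeration throughout, so compare them with 83.5% rather than with the planned 80%.

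**Step 4: add an assumed overlap.** Let f be the share of the 210 who had the exercise component before. Randomisation makes f equal in the two arms on average. The documents give no value for f. Three assumptions about how prior recipients respond:

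- *No further gain*: they improve at 3% in both arms. Intervention rate = 0.15(1 − f) + 0.03f; control rate = 0.03.
- *Half gain*: they improve at 9% in the intervention arm (midway between 3% and 15%) and 3% in the control arm. Intervention rate = 0.15(1 − f) + 0.09f; control rate = 0.03.
- *Full gain in both arms*: they improve at 15% whichever arm they join. Intervention rate = 0.15; control rate = 0.03(1 − f) + 0.15f.

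| f | People of 210 | No further gain: rates, difference | Power | Half gain: power | Full gain in both: power |
|---|---|---|---|---|---|
| 0 | 0 | 15.0% v 3%, 12.0 points | 83.5% | 83.5% | 83.5% |
| 5% | about 10 | 14.4% v 3%, 11.4 points | 80.4% | 82.0% | 77.6% |
| 10% | 21 | 13.8% v 3%, 10.8 points | 76.9% | 80.4% | 71.1% |

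The normal approximation shows a similar fall for the no-further-gain case: 80%, 77% and 74%.

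**Step 5: is a larger overlap credible?** f = 20% needs 42 of the 94 feasibility participants (45%) to enrol, and f = 30% needs 63 (67%). Each would have to belong to a trial practice, attend within the six-month enrolment period, score CFS 4 or 5, meet no exclusion and consent. In the no-further-gain case those shares would give 69% and 59% power, but they are unlikely and should not carry the argument.

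**The case against.** The strongest reply is that the key fact is absent. The protocol names no feasibility practices and does not say that any of them is among the seven trial sites, so overlap may be zero. A reader might infer from the open criteria that carry-over does dilute this trial. The documents support only that it can.

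Four further points stand in whole or in part:

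- **Prior recipients are not fully treated.** Only the exercise component was delivered earlier, before the regime was refined, and the dietary guidance was developed afterwards. Someone randomised to the intervention would still receive something new, which is why the half-gain column is relevant.
- **The persistence data stop at two months.** They do not show that anyone would still be exercising at trial entry. The CFS 4 or 5 requirement would also remove anyone who had improved below that range.
- **The exposed pool is 94.** The workshop members came from the feasibility study and are not extra people. The 24 people in the earlier service evaluation met an exercise regime that is not shown to be this one.
- **This is not bias in favour of an arm.** Randomisation balances prior exposure on average, and adjustment for baseline SHARE-FI absorbs part of any earlier gain in the mixed model. It does not do so in the chi-square test, and it does not remove continued exercise among controls.

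Usual care may itself include physical rehabilitation, so some background exercise is accepted by design. That differs from prior receipt of the programme under test. None of these points closes the gap in the criteria. They limit how much it is likely to matter.

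**Conclusion.** The point holds as a possibility that the plan leaves open, not as an established dilution. The criteria admit people who have already received the exercise component, and the plan neither records nor adjusts for it. If overlap exists, the effect is attenuated towards no difference, and neither arm is favoured.

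The loss depends on an assumed share and an assumed response. With prior recipients at the control rate in both arms, power goes from about 84% to 80% at 5% overlap and 77% at 10%. It is smaller if they still gain from the new components (82% and 80% at half gain), and larger if exposed controls keep improving at the full 15% (78% and 71%), for which the documents offer no evidence. If there is no overlap, nothing is lost. The case for acting rests on how cheaply the gap can be closed, and on the fact that unrecorded exposure cannot be examined afterwards.

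**What to change.** Add one line to the exclusion criteria: previous participation in the feasibility study (including its workshop members), or previous receipt of the study exercise leaflet. Sites check it at screening against the existing list of feasibility participants.

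If an exposed person has already been enrolled, keep them in the intention-to-treat set, record prior exposure as a baseline variable, and run a sensitivity analysis of the primary outcome without them.

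The cost is one amended eligibility line and a slightly smaller recruitment pool, at most about 94 feasibility participants. The sample size of 176 (210 enrolled) does not change.

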### Study methods, assessments and procedures

GP site investigators will undergo three team-based training sessions prior to enrolment, monthly meetings after enrolment and additional ad-hoc meetings when required, led by the principal investigator, in order to standardise the approach and align to this study protocol, including patient communication, intervention delivery and data gathering and management.

Adults attending a GP surgery, meeting the eligibility criteria, will be offered general information about the study by the attending GP. If interested and willing to consent, they will be offered an information leaflet for the trial, and invited to participate. Participants will be randomly assigned to ‘intervention’ or ‘usual care’ parallel arms.

Participants randomly assigned to the usual care group will receive normal primary care, including physical rehabilitation if needed.

Intervention participants will be provided a leaflet with strength exercises and a discussion on how strength exercises have been shown to delay and reverse frailty and build resilience. The information leaflet will have a photographic overview of a home-based exercise regime. They will also be provided with information on post exercise protein consumption as part of a normal balanced diet.

Baseline measurements for all recruited patients will be: age, sex, education, living arrangement (alone, with others), smoking status, alcohol intake, blood pressure, heart rate, BMI (weight and height), comorbidities, malnutrition universal screening tool (MUST), CFS, SHARE-FI (which includes handgrip strength) and bioelectrical impedance for muscle mass, body fat, bone weight, base metabolic rate and ‘biological age’. Bioelectrical impedance will be measured using a Tanita RD 545 Segmental Body Composition Analyser, with dual frequency technology and medical grade accuracy.

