### Method of assigning participants to treatment groups

***Randomisation*.** Randomisation of participants will be done on a 1:1 allocation to intervention or usual care by a simple randomisation procedure, guided by the Clinical Research Centre (CRC) team. We will use a randomisation software product provided by the American National Cancer Institute.

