## Intervention

### Description of intervention

The resistance exercise regime consists of ten, home-based, physical exercises as illustrated in an accompanying leaflet. Each exercise is to be repeated ten times in one minute, increased to fifteen times per minute after about 1 month, when comfortable. A break of 30 seconds is to be taken between sets of exercises. Exercises are to be undertaken at least four times per week and up to every day. Participants should also walk for 30 to 45 minutes, three to four times per week. Participants are advised to consume 1.2 g protein per kg body weight each day. A leaflet will be provided with information on sources of protein, amounts of protein per typical serving and suggested meals. A sample exercise leaflet and protein dietary guidance are shown in
Figure 4 and
Figure 5.

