### Efficacy analysis

Efficacy analysis will be performed on all primary and secondary efficacy endpoints. Point estimates, interval estimates (95% confidence interval) and p-values will be reported.

***Primary efficacy endpoint*.** The primary outcome is Frailty status measured by SHARE-FI at three months of follow-up.

Changes in proportions in non-frail, pre-frail and frail categories will be analysed in both study arms and reported as an odds ratio with associated 95% confidence intervals and tested for significance using a standard chi-square test of proportions.

We hypothesise that participants on resistance exercise regime and with guidance on dietary protein will have a higher SHARE-FI score than patients without this intervention.

This outcome will be analysed as a difference in means between treatment arms using a linear mixed effects model, with arm allocation, SHARE-FI at baseline and age included as fixed effects and GP practice included as a random effect.

***Secondary efficacy endpoints*.** Clinical frailty status measured by CFS at three months will be analysed using a proportional odds mixed model with arm allocation and age as fixed effects and GP practice as random effect. Muscle mass measured by bioelectrical impedance at three months will be analysed using a logistic mixed model with arm allocation as fixed effect and GP practice as random effect.

Ease of the intervention measured on a five-point scale and difference to general health as a result of the exercises measured on a five-point scale will be analysed using a proportional odds model with arm allocation as covariate.

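### Nothing in the entry or allocation rules stops two members of one household from being randomised to opposite arms of a home-based leaflet programme, which could dilute the comparison

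*Protocol article*

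**What the plan says.** **Entry.** The section on selection of the study population states: "All patients aged 65 or older attending the GP site investigator will be screened for eligibility by the GP". It makes eligible anyone who meets all inclusion criteria and no exclusion criterion. The frailty criterion is "Rockwood clinical frailty scale score 4 or 5 (vulnerable or mildly frail". Neither list mentions a second member of the same household.

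**Allocation.** The randomisation section states: "Randomisation of participants will be done on a 1:1 allocation to intervention or usual care by a simple randomisation procedure". It has no rule for couples or housemates.

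**Intervention.** The description of the intervention states: "The resistance exercise regime consists of ten, home-based, physical exercises as illustrated in an accompanying leaflet". On diet it adds: "A leaflet will be provided with information on sources of protein, amounts of protein per typical serving and suggested meals".

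**Data and model.** The baseline list includes "living arrangement (alone, with others" but no item on whether a housemate is also in the trial. The primary mixed model has "GP practice included as a random effect" and no household term.

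**Sample size.** The calculation assumes 15% improvement to non-frail with the intervention and 3% in control (an allowance for bias), type I error 5% and power 80%. This gives 176 evaluable participants, and 210 enrolled to allow for 15% drop-out.

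**The concern.** Both parts of the programme are paper materials used in the home. If one partner is allocated to the intervention and the other to usual care, the exercise leaflet lies in the house they share and the suggested meals may be cooked for both. The usual-care partner may then take up part of the programme.

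In an intention-to-treat comparison this raises the control response and shrinks the observed difference. The sample size has no slack to absorb such a loss. The conduct described would not show it either: only intervention participants are telephoned and asked about exercise and diet, and the listed trial data do not record co-enrolment.

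**Working it through.** **1. Reproduce the plan's figure.** Inputs from the sample size section: p1 = 0.15, p2 = 0.03, 1:1 allocation, alpha 0.05 (taken as two-sided; the protocol does not say), power 0.80. Use the two-proportion formula with pooled variance under the null and no continuity correction, and mean proportion 0.09:

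n per arm = [1.96 × √(2 × 0.09 × 0.91) + 0.8416 × √(0.15 × 0.85 + 0.03 × 0.97)]² / 0.12²
= [1.96 × 0.4047 + 0.8416 × 0.3957]² / 0.0144 = 88.1

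This gives 176 if rounded down and 178 if rounded up. With drop-out, 176/0.85 = 207.1 (208) and 178/0.85 = 209.4 (210). The stated 176 and 210 are reproduced to within rounding.

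**2. Planned power at 88 per arm.** (0.12 × √88 − 1.96 × 0.4047) / 0.3957 = 0.840, so power is 80.0%.

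**3. Dilution model.** Let f be the share of participants with a co-enrolled housemate and r the share of the 12-point effect passed on to an exposed usual-care participant. The documents give neither, so both are assumptions. Under simple 1:1 allocation a housemate is in the other arm with probability 1/2. Hence:

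control rate = 3% + (f/2) × r × 12 points

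Example with f = 10% and r = 1: 3% + 0.05 × 12 = 3.6%. The difference becomes 11.4 points. (0.114 × √88 − 1.96 × 0.4107) / 0.4027 = 0.656, so power is 74.4%.

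**4. Results at 88 per arm, intervention rate held at 15%.** Cells show the control rate, then power.

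| f | usual care exposed | r = 0.25 | r = 0.5 | r = 1 |
|---|---|---|---|---|
| 5% | 2.5% | 3.08%, 79.3% | 3.15%, 78.6% | 3.3%, 77.3% |
| 10% | 5% | 3.15%, 78.6% | 3.3%, 77.3% | 3.6%, 74.4% |
| 20% | 10% | 3.3%, 77.3% | 3.6%, 74.4% | 4.2%, 68.4% |

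**5. What the scenarios mean in people.** f = 5% is 0.05 × 210 = 10.5 participants, or about five pairs, with two or three exposed among 105 usual-care participants (0.025 × 105 = 2.6). f = 20% is 42 participants, or 21 pairs: three per practice across seven practices of about 30 participants each.

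These powers refer to the comparison of proportions on which the trial was sized. The mixed model for mean SHARE-FI would be diluted in the same direction, but the protocol gives no standard deviation from which to compute a loss.

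**The case against.** **This is an article, and couples may be handled in site training.** That is possible. But eligibility and the unit of allocation are design elements that the article does state, and followed as written they admit split households.

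**The upper scenarios are unlikely.** Both partners must be 65 or older, score 4 or 5 on the frailty scale, pass every exclusion, attend a site investigator within six months, and consent. Full transfer is also unlikely: in the feasibility study, people given the exercises directly had two-month compliance of only 65% without a prior call and 78% with one. This stands, and it makes the right-hand column and bottom row of the table outer bounds. In the other direction, feasibility uptake was 95% in women and 78% in men. If it carried over and were independent within couples, 0.95 × 0.78 = 74% of couples with both partners eligible would enrol together.

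**The 3% control rate already allows for bias.** It does, but it is not tied to household sharing and is already part of the 80% baseline.

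**Any bias is towards no effect.** True. It cannot create a false positive; what is at stake is a missed or understated benefit.

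A reader might infer two stronger points, and neither holds:

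- *That partners' correlated outcomes invalidate models without a household term.* Partners are randomised independently. Pairs in the same arm raise the variance of the arm difference, split pairs lower it, and in expectation the two cancel. With 20% of participants in pairs and pairing ignored, simulated type I error was 4.9% to 5.4%.
- *That exposed participants could never be identified.* Living arrangement rules out those who live alone, and each centre keeps signed consent forms and identifying documents, so housemates could be matched at site. The accurate statement is only that the listed trial data do not record co-enrolment.

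**Conclusion.** The point holds as a risk that the design leaves open. The entry and allocation rules allow housemates to be split between arms, about half of co-enrolled pairs would be, and the materials are easily shared at home. Any resulting bias runs towards no effect.

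It would go too far to say that usual-care partners are in fact exposed or that the effect is in fact diluted, because the documents contain no rate for either. On the stated assumptions the loss ranges from under 1 power point (f = 5%, r = 0.25) to about 12 (f = 20%, r = 1). With a quarter to half of the effect passed on and 5% to 10% co-enrolled, it is about 1 to 3 points. This is a cheap improvement to make before enrolment, not a flaw that undermines the trial.

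**What to change.** Add to the eligibility criteria that only one person per household may be enrolled, namely the first to consent. Add a screening question on whether anyone in the home is already in the trial. The planned 15% versus 3% contrast is then protected from this source and the enrolment target stays at 210.

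The cost is one eligibility line, one question, and some eligible partners turned away. They must be replaced within the six-month enrolment period, in a trial that may stop if less than half the sample is enrolled after six months. In the 20% scenario that is 21 people; in the 5% scenario, about five.

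An alternative that keeps partners in is to allocate households as units. With an assumed within-household correlation of 0.3 and 5% to 30% co-enrolled, the design effect 1 + f × 0.3 is 1.015 to 1.09. That requires about 181 to 195 evaluable (178 × 1.015 to 178 × 1.09) and 213 to 230 enrolled (divided by 0.85). If neither change is made, co-enrolled housemates should at least be recorded.
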